#### Patients with SPMS

For the patients with SPMS subpopulation, the primary analysis will be carried out with a test on proportions, comparing the proportion of subjects in the two arms who will be classified as “improved” with respect to the clinical end point (α = 5%, two-sided test). A multivariate analysis based on a logistic regression model will be carried out, taking into account relevant factors, such as gender, time from MS diagnosis, concomitant treatments and EDSS at baseline. A secondary analysis of treatment effect will also be performed by comparing the distribution of each category of the combined end point in the two treatment groups. The treatment effect on each single functional parameter of the combined end point will also be assessed using the Hochberg correction for multiple testing
[54]. The MRI end point will be evaluated by comparing the mean number of lesions at 1 year, assuming a negative binomial model (α = 5%, two-sided LRT). In both samples (RRMS and SPMS), analyses will be performed on all secondary end points. Any deviation from the planned statistical methods will be properly documented in the study report.

### Stopping Rules

Guidelines have been established to ensure that the study will be stopped as soon as possible in the event of occurrence of an unacceptable proportion of SAEs. The method used follows a Bayesian approach
[55,56]. It is assumed that the number of events follows a binomial distribution, and the *a priori* distribution of the probability of event is a β (1,1), which corresponds to an uninformative uniform distribution. Table 
6 shows the experimental results that provide a posterior probability of 90% or more of observing a percentage of SAEs in the overall sample higher than an acceptable maximum, established at 4%. Given the current number of recruited patients, the values in Table 
6 indicate the minimum number of SAEs that should alert the investigators to assess whether to continue the study.

**Table 6 T6:** Safety results that provide a posterior probability of 90% or more of observing a percentage of serious adverse events in the overall sample higher than an acceptable maximum (4%)

**Number of serious adverse events**	**Number of cumulative patients in study**
2	13 to 27
3	28 to 44
4	45 to 61
5	62 to 79
6	80 to 98
7	99 to 117
8	118 to 137
9	138 to 157
10	158 to 177
11	178 to 198
12	199 to 218
13	219 to 239
14	240 to 260
15	261 to 281
16	282 to 302
17	303 to 323
18	324 to 345
19	346 to 366
20	367 to 388
21	389 to 410
22	411 to 431
23	432 to 453
24	454 to 475
25	476 to 497
26	498 to 519
27	520 to 541
28	542 to 563
29	564 to 585
30	586 to 608
31	609 to 630
32	631 to 652
33	653 to 674
34	675 to 679

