#### Patients with RRMS

The sample size was estimated on the basis of the primary end point on MRI. We assume that the average total number of MRI active lesions in the control group is equal to 6 with a standard deviation of 7.6
[53]. The intention-to-treat (ITT) analysis of 423 patients, allocated into the two treatment arms according to a randomization ratio of 1:2 (141 in the control arm and 282 in the experimental arm), will allow us to detect an absolute mean reduction of 2.1 lesions with an α error of 0.05 (two-sided likelihood ratio test (LRT)) and a power of 90% (power analysis based on 5,000 simulations, assuming a negative binomial distribution). Thus, we will be able to highlight a 1-year mean reduction from 6 lesions in the control arm to 3.9 in the experimental arm, which corresponds to a relative reduction of 35%. Even in the presence of a higher level of variability, with a standard deviation of nine lesions, our study would have a power of 81%, to show as statistically significant the same difference. This sample size will also be able to show a reduction of at least 0.3 in the annualized relapse rate with a power greater than 93%, (0.6 vs. 0.9 in the control arm, α = 0.05, two-sided LRT). The sample size of 423 patients is also adequate for the evaluation of the combined clinical end point with a 92% power or higher to detect a 15% increase in the percentage of improved patients (with a 5% to 15% figure in the control arm, α=0.05, two-sided test on proportions). To obtain a sample size of 423, a total of 445 patients will be recruited (148 in the control arm and 297 in the experimental arm), to take into account a 5% dropout rate, leading to nonevaluation of the primary end point at 12 months.

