### Adverse events

All subjects will be monitored throughout the study for adverse events (AEs). Possible AEs related to this study are (1) allergic reactions or hypersensitivity to the contrast medium (immediate or delayed), such as nausea, vomiting (even prolonged), itching, hives, bronchial spasm (3% of cases); (2) slight local pain (40% of cases) or headache (10%) during dilatation of the veins; (3) minor bleeding with local hematoma at the injection site (5% of cases), nausea and lowering of arterial pressure (0.2%) during cannulation of the femoral vein; and (4) postoperative headache. Possible serious AEs (SAEs) are (1) allergic reactions or hypersensitivity to the contrast medium (immediate or delayed), such as hypertensive shock, pulmonary edema or cardiorespiratory arrest (1 patient in 1,000); and (2) venous thrombosis or rupturing of the vein with postoperative hemorrhage (3% to 4% of cases). Unexpected AEs can also occur as a result of technical difficulties during the venographic and angioplastic procedures. All AEs or SAEs will be reported to the Safety Surveillance Unit/Institutional Review Board (SSU/IRB) that approved the protocol, unless otherwise required and documented by the SSU/IRB. All AEs or SAEs will be reported in the e-CRF.

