### Study reports

The scientific responsibility for monitoring the course of the study will be entrusted to an independent data monitoring committee (IDMC) and to the SC that will work in close contact with the DCC and the CRO. The IDMC will receive a report to evaluate the progress and safety of the study every 3 months in the first year and every 4 months from the second year on, and it will inform the SC of any recommendations for an early interruption of the study. The reporting form will be defined in collaboration with the DCC and the CRO, it will be approved by SC and it will be produced by the CRO in a blinded form. Only the IDCM and the party responsible for the quality of the data may ask for an unblinded version of the report. The IDMC will evaluate safety, also taking into account early stopping rules. The IDMC will also consider whether the proportion of negative venography in the patients with positive echo Doppler results exceeds the expected 10% proportion and will discuss with the SC the possible implications for the conduct of the study. Every 4 months the DCC will provide an evaluation of study quality. Within 1.5 years after the start of recruitment, the DCC member in charge of monitoring study quality will provide a description of preliminary results on the subset of patients with 1 year of follow-up, allowing assessment of the validity of the sample size calculations. This evaluation will be submitted in blinded fashion to the IDMC for recommendations to the SC. During the study, the IDMC, in collaboration with the SC, will assess new publications on CCSVI and MS that might be relevant to the study protocol.

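### The 4% SAE alert in Table 6 is set on sham and PTA patients pooled, so if sham SAEs are near zero it corresponds to up to about 6% in the PTA arm

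*Protocol article*

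**What the plan says.** Stopping Rules in the protocol article uses a binomial model for SAEs. The prior "distribution of the probability of event is a β (1,1), which corresponds to an uninformative uniform distribution". Table 6 lists "the experimental results that provide a posterior probability of 90% or more" for "observing a percentage of SAEs in the overall sample higher than an acceptable maximum, established at 4" (per cent). Its second column is headed "Number of cumulative patients in study" and ends at 679. The tabulated values "indicate the minimum number of SAEs that should alert the investigators to assess whether to continue the study", so they prompt a review and do not stop the trial.

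The 679 are both arms together. Sample size gives "148 in the control arm and 297 in the experimental arm" for RRMS, and 78 and 156 for SPMS. Under Interventions, sham patients have catheter venography and a simulated angioplasty.

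Adverse events lists two kinds of possible SAE: severe contrast reactions (1 in 1,000), and "venous thrombosis or rupturing of the vein with postoperative hemorrhage (3% to 4% of cases"). Neither figure is split by arm.

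Under Study reports, the monitoring committee receives a periodic report, and "it will be produced by the CRO in a blinded form". The committee may ask for an unblinded version. No threshold for a single arm appears anywhere in the article.

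**The concern.** The rule is meant to raise the alarm early if serious harm is too frequent. The exposure that separates the arms is balloon dilatation, and one third of the denominator does not have it. If PTA raises the SAE rate and sham does not, the sham patients dilute the observed proportion. A 4% limit on the whole sample is then a higher limit for the patients actually treated.

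Table 6 is the only numerical safety trigger in the article. A diluted trigger means that more patients could undergo an invasive procedure, whose benefit the Background calls unproven, before anyone is formally prompted to reassess. It is also unclear what the 4% means. It sits at the upper end of the 3% to 4% given for thrombosis or rupture, yet the text does not say whether that expectation concerns PTA patients or everyone.

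**Working it through.** **1. Table 6 reproduces.** With *s* SAEs in *n* patients, the posterior is Beta(1+*s*, 1+*n*−*s*), and the alert needs P(rate > 4%) ≥ 0.90.

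- 2 SAEs in 27 patients: 0.900.
- 10 in 177: 0.897.
- 20 in 388: 0.896.
- 34 in 679: 0.920.

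A strict 0.90 gives upper row limits at most 4 patients below the printed ones, except the last row, which ends at the planned total of 679. Every printed upper limit has a posterior of at least 0.895, so the table fits a posterior rounded to 0.90. Its arithmetic is not in question.

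**2. Arm sizes.** Sham 148 + 78 = 226; PTA 297 + 156 = 453; total 679.

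**3. What a pooled 4% means for the PTA arm.** PTA rate = (0.04 × 679 − sham rate × 226) / 453. The sham rate is an assumption.

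| Assumed sham SAE rate | PTA rate at a pooled 4% |
|---|---|
| 0% | 27.16/453 = 6.0% |
| 0.1% (the contrast-reaction figure) | 5.95% |
| 1% | 5.5% |
| 2% | 5.0% |
| 4% | 4.0% |

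**4. Where the alert fires.** The 90% requirement puts the alert above a pooled 4%. At full enrolment it needs 34 SAEs: 34/679 = 5.0% pooled, or 34/453 = 7.5% of PTA patients if all occur there. On the same assumption, 20 SAEs in 388 patients are 7.7% of PTA patients, and 10 in 177 are 8.5%. The same rule on 453 PTA patients alerts at 23 SAEs by the printed rows (5.1%) or 24 at a strict 0.90 (5.3%).

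**5. Chance that the alert ever fires.** Simulation of 20,000 trials of 679 patients at 2:1, with the boundary as printed and 0% SAEs in sham. The article does not say how often the table is consulted. It gives a threshold at every *n* from 13, so one reading checks after every patient. The other, four looks at 170, 340, 509 and 679, is an assumed schedule.

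| True PTA rate | Every patient: pooled / PTA only | Four looks: pooled / PTA only |
|---|---|---|
| 5% | 39% / 81% | 9% / 63% |
| 6% | 57% / 94% | 26% / 88% |
| 7% | 77% / 99% | 53% / 97% |

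The gap narrows as sham SAEs rise. With PTA at 6% and a check after every patient, the pooled alert fires in 68%, 78% and 85% of trials for sham rates of 1%, 2% and 3%, against about 94% for PTA only. With four looks and sham at 1% or 2%, it fires in 40% or 54%, against 88%.

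**6. Cost of reading the boundary on PTA patients only.** At a true PTA rate of 3% or 4%, it alerts in about 30% or 55% of trials when checked after every patient, and in about 7% or 29% with four looks.

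**The case against.** The strongest reply is that the sponsor deliberately set the limit for the whole sample, that nothing is miscalculated, and that oversight does not rest on the table alone. The committee reviews safety every 3 months in the first year, takes the stopping rules into account among other things, and can ask for unblinded data. The committee's charter and the full protocol are not shown and may provide for reporting by arm.

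The size also depends on assumptions. SAEs are counted over the whole study without restriction to procedural events. Sham patients have femoral catheterisation, contrast and three weeks of heparin, so their rate need not be near zero. The article does not attribute its 3% to 4% to dilatation. Finally, moving an unchanged 4% limit to the PTA arm makes the rule stricter, with frequent alerts at rates the protocol appears to expect.

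Most of this stands, and it limits the point. A reader might infer that the rule is blind to PTA harm, or that the PTA arm will reach 6% before anything happens. The documents support neither: 6% is a ceiling under an assumption, and the committee may look by arm at any time. The low four-look percentages belong to an assumed schedule and should not be quoted alone.

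Two things remain. The option to ask for unblinded data sets no arm-level threshold. And the alert frequency at 4% comes largely from checking this boundary after every patient: the pooled rule fires in about 58% of trials when both arms have a true rate of 4%.

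**Conclusion.** The point holds as a weakness of design, and it should be fixed. Pooling is explicit in the text and raises the effective limit for PTA patients to at most about 6.0%. The dilution disappears only if the sham SAE rate equals the PTA rate. For a true 6% PTA rate and no sham SAEs, the chance of an alert falls from 94% to 57% with a check after every patient, or from 88% to 26% with four assumed looks.

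These figures rest on the planned 2:1 allocation, on assumed SAE rates by arm, and on an assumed frequency of checking. They do not show that the 4% limit is wrong or which population it ought to bind. That is a safety judgement for the sponsor and the monitoring committee. Because the table only prompts an assessment and unblinded review is available, the point does not make the safety plan untenable.

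**What to change.** - Give the monitoring committee SAE counts by arm routinely, in a closed report, and not only on request.
- Keep the Beta(1,1) prior and the 90% posterior probability. Beside the pooled quantity, compute the same one on PTA patients: numerator, patients with an SAE after PTA; denominator, patients who have had PTA.
- Have the sponsor and the committee state whether the 4% maximum is meant for PTA patients or for both arms together, and reconcile it with the 3% to 4% under Adverse events, saying which patients that figure describes.
- State how often Table 6 is consulted, since the alert frequency depends heavily on it.

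The cost is wording in the protocol and the committee's charter, plus one extra table in a report that the committee can already obtain unblinded. If the unchanged boundary is also read on PTA patients, there will be more alerts at tolerated rates (step 6 of the working), each leading to an assessment and not to a stop.

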### Concomitant therapies

If not explicitly mentioned in the inclusion or exclusion criteria, the concomitant therapies for chronic pathologies not correlated with MS will be continued throughout the study period. All drugs given to participants during the study will be recorded in the e-CRF. All pharmacological or rehabilitative treatments (motor reeducation and balance, walking and cognitive training), carried out during the study and in the six months previous randomization will be recorded in the e-CRF. Changes considered in the regimen of treatments with potentially relevant effects on the tested functions (for example, changes in type and intensity of physiotherapy, new assumption of antispastic drugs) will be recorded and taken into account in the data analyses. The implantation of a baclofen pump will lead to the classification of the patient as “worsened.”

### Monitoring of the study

The monitoring procedures will be entrusted to a CRO. During the study, monitoring personnel will visit the participating centers on a regular basis to verify completeness of the data, accuracy of completion of the data collection forms, adherence to the study protocol and to good clinical practice (GCP), and state of the enrollment or any other problems. The treating neurologist will provide the monitors with full access to clinical data to confirm the consistency of the information recorded on the e-CRF. All information relative to patient identity must be kept confidential according to Italian law (D. Lvo 96/2003). Participants will be identified on the e-CRF only by a conventional code to keep their personal and sensitive information anonymous.

### Study reports

The scientific responsibility for monitoring the course of the study will be entrusted to an independent data monitoring committee (IDMC) and to the SC that will work in close contact with the DCC and the CRO. The IDMC will receive a report to evaluate the progress and safety of the study every 3 months in the first year and every 4 months from the second year on, and it will inform the SC of any recommendations for an early interruption of the study. The reporting form will be defined in collaboration with the DCC and the CRO, it will be approved by SC and it will be produced by the CRO in a blinded form. Only the IDCM and the party responsible for the quality of the data may ask for an unblinded version of the report. The IDMC will evaluate safety, also taking into account early stopping rules. The IDMC will also consider whether the proportion of negative venography in the patients with positive echo Doppler results exceeds the expected 10% proportion and will discuss with the SC the possible implications for the conduct of the study. Every 4 months the DCC will provide an evaluation of study quality. Within 1.5 years after the start of recruitment, the DCC member in charge of monitoring study quality will provide a description of preliminary results on the subset of patients with 1 year of follow-up, allowing assessment of the validity of the sample size calculations. This evaluation will be submitted in blinded fashion to the IDMC for recommendations to the SC. During the study, the IDMC, in collaboration with the SC, will assess new publications on CCSVI and MS that might be relevant to the study protocol.

## Discussion

In this trial, we aim to evaluate the efficacy and safety of angioplasty of extracranial veins for patients with RRMS or SPMS as well as sonologic diagnosis of CCSVI. Such a study may be seen as controversial because the pathophysiological evidence of the cause-and-effect relationship between CCSVI and MS is lacking. Had this been a typical situation, without strong media pressure
[57], a phase III comparative randomized trial at this stage probably would not have been justified and we would have proceeded with a phase II study. However, a phase II trial would likely have been done without a control group and the sample sizes would have been too small, given the variability of MS course, to indicate plausible effects. It would thus add little to what we know from observational studies and leave the question of efficacy still in need of a rigorous phase III trial.

MS is widely considered an inflammatory autoimmune disease; however, this remains a hypothesis, and in reality the exact cause of MS remains unknown. The pharmacological treatments currently available for MS can modify, to a limited degree and over the long term, the natural history of the disease. However, they cause numerous side effects and are, at the moment, not easily proposable along the whole disease course, which corresponds to the rest of the patient’s life. Currently, there are no elements for evaluating whether new drugs under review for approval or in the experimentation phase will be able to change the natural history of MS. Thus it is understandable that a nonpharmacological treatment hypothesizing an improvement in the clinical picture (that is, the intervention proposed by Zamboni), arouses great expectations for a confirmation of its scientific validity.

The proponent group took into account that the end points currently used in clinical pharmacological studies have been criticized on both clinical and methodological grounds
[58,59]. For this reason, two primary end points were identified, one defined by a set of clinical instrumental parameters related to specific functional deficits experienced by patients with MS and the other one based on MRI findings, both measured 12 months after randomization. The decision to utilize two primary end points emerged from various considerations. First, the hypothesized effect of angioplasty for MS patients with CCSVI does not allow exclusion of a clinical effect independent of the incidence of active MRI lesions. On the other hand, MRI parameters are largely utilized as indicators of activity in clinical trials for MS and are considered robust with respect to any placebo effect. The observation of a statistically significant advantage in only one of the two end points (clinical or MRI) will be sufficient to declare the study results in favor of the superiority of angioplasty over sham procedure. In the event of conflicting results (active treatment favored by one end point and not favored by the other one), the combined clinical end point will prevail. Second, the use of two primary end points in this situation offers at least two advantages: (1) If masking of both participants and investigators succeeds, the demonstration of a significant effect of the treatment on even only one of the two end points would be sufficient to reject the hypothesis that venous angioplasty is not active or efficacious in patients with MS; and (2) in the event that failure of the masking occurs, thus potentially weakening the evidence coming from the clinical end point, the evaluation of the MRI end point would maintain its validity entirely, thereby permitting the study to conserve, even if only partially, scientific and clinical usefulness.

A novel functional composite end point was defined to assess the primary clinical end point. The reason for this decision was that the EDSS
[47], the most widely used disability measure in clinical trials for MS, is an ambulation-centered scale that does not take into account cognitive impairment or upper-arm or bladder dysfunctions that are primary components of disability. The EDSS is an ordinal nonlinear scale whose serial upward changes of 0.5 or 1.0 points, confirmed at 3–6 months or unconfirmed, are commonly used in clinical trials. However, changes of 0.5 points are invalid, even if confirmed at 3 or 6 months, and, similarly, 1-point changes are not significantly more likely to occur for worsening than for improvement
[58]. When choosing the indicators of the functional composite end point, we took into account relevant parameters, that is, the prevalence and clinical relevance of impaired functions in MS, objective and validated measures, and global feasibility of the tests in terms of tolerance, time scales, costs and necessary skills. Also, all tests are instrumental and thus semiobjective, although prone to behavioral influences. An extensive review of the literature was carried out, and the specific skills and experience in the field of functional testing of the various members of the working group were taken into account. The choice was then made after reflection and collegial discussion.

Each participating center is accredited as a MS center by the National Health Service and employs professionals with the following skills: neurology, neuroradiology, noninvasive vascular diagnosis, vascular surgical radiology, physiotherapy and psychometric testing. The staff participating in the study are accredited for the ECD diagnosis of CCSVI, the venous angioplasty intervention and the measurement of the functional end points.

This clinical trial will provide answers with regard not only to the efficacy of venous angioplasty on the inflammatory component of MS but also about subjective symptoms and functions, such as motor impairments, sphincteral and visual deficits, fatigue, anxiety, depression and attention deficits, which are meaningful clinical outcomes. In fact, an important part of patients’ expectations, sustained and amplified by anecdotal data on improvement of quality of life reported in the Zamboni *et al*. study
[34], has to do with precisely these aspects.

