#### Patients with SPMS

This combined clinical end point is being used, to the best of our knowledge, for the first time in this trial. Thus, the power of the study was calculated under various scenarios concerning different values of the 12 months percentage of improvement in either group. The main analysis concerns the probability of improvement, considering the worsened, the stable and the fluctuating conditions as failures. With an enrolment of 222 patients allocated according to a randomization ratio of 1:2 (74 in control arm and 148 in experimental arm), power is sufficient to detect, based on the ITT analysis, an absolute improvement ranging from 15% to 25% (α = 0.05, two-sided test on proportions), as shown in Table 
4. In order to obtain a sample size of 222, a total of 234 patients will be recruited (78 in the control arm and 156 in the experimental arm), taking into account a 5% of drop-out due to lack of evaluation at 12 months.

**Table 4 T4:** Power calculation for different scenarios of baseline values and deltas of the probability of improvement at 1 year in the combined clinical end point (intention-to-treat analysis)

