### Statistical analyses

The DCC will be responsible for the statistical analysis at the end of the study. Analysis will be performed blinded to the treatment allocation. The main analysis will be conducted according to the principles of ITT, separately on the two subpopulations (RRMS and SPMS), which implies that all randomized patients will be retained in the original randomized arm. The secondary analysis will be run per protocol (PP) and will take into consideration all randomized patients who were positive (true CCSVI) also at the time of venography. It is expected that the false-positives will be at most 10%. Dropout cases (missing data at both the 12-month assessment and the 3-month extension) will be excluded from both the ITT and the PP analyses. We expect ≤5% dropout cases. The impact of missing data will be evaluated by sensitivity analysis. Both the ITT and PP analyses will also be conducted across the whole study sample (RRMS and SPMS).

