#### Patients with RRMS

In this group of patients, the evaluation of the treatment effect on the MRI primary end point (average number of lesions on MRI at 1 year) will be performed using a LRT, assuming a negative binomial model (α = 5%, two-sided test). This comparison will also be evaluated using a regression model, adjusting for some important factors, that is, time from diagnosis of MS disease, concomitant treatments and EDSS at baseline. A descriptive analysis will also be conducted on the components of this primary end point, considering separately the treatment effect on T1 active lesions and on new or enlarging T2 lesions. The effect of the treatment will also be assessed on the clinical end point, comparing the proportions of patients classified as “improved,” as defined in the “primary end point” section (α = 5%, two-sided test on proportions). The relapse rate (secondary end point) in the two treatment groups will be compared by means of a LRT, assuming a Poisson model (also adjusting for the same factors considered for the primary end point). The Poisson model assumptions will be assessed, and, in the event of evidence of overdispersion, alternative models that relax these assumptions will be considered (that is, mixed-effects Poisson model).

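### Either primary end point can carry the superiority claim, yet each is tested at a full two-sided 5%, so within one population the false-positive rate is up to about 9.75% (4.9% rather than 2.5% in favour of angioplasty)

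*Protocol article*

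**What the plan says.** **Decision rule (Discussion).** Of the two primary end points, "The observation of a statistically significant advantage in only one of the two end points (clinical or MRI) will be sufficient to declare" in favour of angioplasty. The next sentence adds a tie-break: "In the event of conflicting results (active treatment favored by one end point and not favored by the other one), the combined clinical end point" is to prevail. No significance level goes with either sentence.

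**Test levels (Statistical analyses).**
- RRMS, MRI: a likelihood ratio test, "assuming a negative binomial model (α = 5%, two-sided test".
- RRMS, clinical: "α = 5%, two-sided test on proportions".
- SPMS, clinical, called the primary analysis there: "with respect to the clinical end point (α = 5%, two-sided test".
- SPMS, MRI: "assuming a negative binomial model (α = 5%, two-sided LRT".

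**Populations.** The main analysis is run separately in RRMS and SPMS. In addition, "Both the ITT and PP analyses will also be conducted across the whole study sample (RRMS and SPMS" combined, without a level or a part in the decision.

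**Correction for multiple tests.** The only one named is Hochberg, in the SPMS analysis section, for the single functional parameters of the composite.

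**Powers (Sample size).** The RRMS MRI power (90%), the RRMS clinical power (92% or higher) and the SPMS powers in Table 4 are all computed at an undivided 0.05.

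**The concern.** When either of two tests can carry the conclusion and each uses the whole 5%, the error rate of the conclusion is not 5%. The article fixes all three elements itself: the either-or rule, the level of each test, and the power at that level. This is therefore not a detail left to an unseen analysis plan; a plan that divided alpha would contradict the levels and powers printed here.

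At stake is the trial's main claim. The Discussion concedes that evidence for a causal link between the venous condition and MS is lacking, and the Adverse events section expects venous thrombosis or vein rupture in 3% to 4% of cases. In that setting a chance of false superiority close to twice the nominal one is material. It is also hard to repair after unblinding, when any choice of correction can look data-driven.

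**Working it through.** **1. The plan's own powers.**

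*RRMS MRI.* Inputs (Sample size, Patients with RRMS): means 6 and 3.9, control SD 7.6, 141 and 282 patients.
- Dispersion k = (7.6² − 6)/6² = 1.438, assumed common to both arms.
- SE of the log rate ratio = √[(1/6 + 1.438)/141 + (1/3.9 + 1.438)/282] = 0.132.
- ln(6/3.9) = 0.431, and 0.431/0.132 = 3.267 (unrounded inputs).
- Power = Φ(3.267 − 1.960) = 0.904. Simulating 5,000 trials with the likelihood ratio test gives 0.903. Stated: 90%.

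*RRMS clinical, least favourable case, 15% v 30%.* Normal approximation with continuity correction.
- Corrected difference = 0.15 − ½(1/141 + 1/282) = 0.1447. Null SE 0.0447, alternative SE 0.0406.
- Power = Φ[(0.1447 − 1.960 × 0.0447)/0.0406] = 0.920. Stated: 92%.

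*SPMS.* The same formula with 74 and 148 patients gives 0.83/0.72/0.63 for the 15-point row of Table 4 (stated 0.84/0.72/0.64). All nine cells agree within 0.02.

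So the stated powers do rest on an undivided 5%.

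**2. Error rate within one population (two end points, no true effect).**

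Independent end points:
- Either direction: 1 − 0.95² = 9.75%.
- In favour of angioplasty: 1 − 0.975² = 4.9%, against 2.5% for one test.

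The article gives no correlation between the end points. For bivariate normal test statistics:

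| Assumed correlation | Either direction | In favour |
|---|---|---|
| 0 | 9.75% | 4.9% |
| 0.5 | 9.1% | 4.5% |
| 0.8 | 7.8% | 3.9% |

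**3. The conflict rule (independent end points, in favour).**
- A significantly adverse clinical result blocks an MRI win: 0.025 + 0.025 × 0.95 = 4.9%.
- Any adverse clinical estimate blocks it: 0.025 + 0.025 × 0.475 = 3.7%.

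Both exceed 2.5%.

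**4. Both populations, if a win in either counts.** The patients are disjoint, so the populations are independent.
- Either direction: 1 − 0.95⁴ = 18.5%; in favour: 1 − 0.975⁴ = 9.6%.
- At correlation 0.5 between end points: 17.3% and 8.9%.

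**5. After correction, at the planned sample size.** A 2.5% + 2.5% split holds the rate within a population at 5% or less (1 − 0.975² = 4.94% if independent). Two-sided 2.5% uses z = 2.241.
- RRMS MRI: Φ(3.267 − 2.241) = 0.847 (0.844 by simulation). With Hochberg, if only MRI responds: 0.847 + 0.05 × (0.904 − 0.847) = 0.850.
- RRMS clinical, control 5%/10%/15%: 98%/93%/86%, from 99%/96%/92%.
- SPMS clinical, 15-point row: 0.73/0.60/0.51.

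**The case against.** **The conflict rule ranks the end points.** It is part of the decision rule and has to be counted. On the reading most favourable to the plan that still lets an MRI result win alone, it lowers the rate to 3.7% in favour, which is a reduction but not control. If an end point is not favoured whenever it is non-significant, a lone MRI win could never stand. The rate would then be 2.5%, but the rule would cancel the sentence before it. The article cannot mean both.

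**Each population has its own lead end point.** The RRMS sample size rests on MRI, and the SPMS section calls the clinical test primary. One could read the plan as a single primary test per population. The Discussion does not allow this: it makes either end point sufficient and draws no distinction by population. Even on that reading, two tests in disjoint patients give 1 − 0.95² = 9.75% if either may carry the claim.

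**Stronger readings.** A reader might count six tests, adding the pooled sample, and arrive at about 21%. The article does not support that: the pooled analysis has no stated level and no role in the declaration. Nor does it say that a win in SPMS alone would be the trial's conclusion; it describes SPMS results as preliminary, and whether two disjoint populations need joint control is debatable. The 18.5% is therefore conditional. Finally, two-sided rates also count results against angioplasty. A superiority claim needs an advantage, so 4.9% against 2.5% is the closer match to the claim itself.

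**Conclusion.** The point stands for the two primary end points within a population. As written, the rule gives up to about 9.75% in either direction instead of 5%, and up to 4.9% instead of 2.5% for a false claim in favour of angioplasty. These are the values under independence. Positive correlation lowers them, to 7.8% and 3.9% at an assumed 0.8, and the excess vanishes only if the two end points are perfectly correlated. The conflict rule allocates no alpha and leaves at least 3.7% in favour under independence, unless it is read so as to annul the either-or rule.

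The 18.5% (9.6% in favour) applies only if a win in either RRMS or SPMS counts, which the article should settle. This should be corrected before unblinding, because it concerns the rule by which the trial declares success.

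**What to change.** 1. **Statistical analyses, RRMS and SPMS.** Apply Hochberg, already cited, to the two primary end points within each population at a family-wise two-sided 5%. A fixed 2.5%/2.5% split is the alternative that needs no assumption about their dependence.
2. **Discussion.** Define a statistically significant advantage as one that is significant after that correction, and say what makes results conflicting: a significantly adverse clinical result, an adverse estimate, or mere non-significance.
3. **Populations.** State which population carries the superiority declaration, and that the pooled analysis is supportive. If a win in either population may carry it, control within each still leaves 1 − 0.95² = 9.75% overall, so alpha must also be shared between populations. SPMS need not be barred from a claim of its own.
4. **Sample size and Table 4.** Restate the powers at the corrected level.

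**Cost.** No extra patients if the lower power is accepted: RRMS MRI about 85% rather than 90%, RRMS clinical 86% rather than 92% in the least favourable case, and the SPMS 15-point row down by 0.11 to 0.13. Hochberg recovers part of this when both end points respond. Keeping 90% for RRMS MRI at 2.5% would need 423 × [(2.241 + 1.282)/(1.960 + 1.282)]² ≈ 500 evaluable patients, or about 526 recruited at 5% dropout, instead of 445.
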